#### 2.2.3. Exclusion Criteria

The participants are not eligible to participate in the trial if they meet any of the following criteria: (1) have acute viral pharyngitis and laryngitis, acute herpes angina, acute conjunctivitis pharynx, or acute tonsillitis, suspected influenza, and vaccination against influenza within 21 days before enrollment; (2) history of severe cardiovascular, pulmonary, renal or haematopoietic system disease, immunodeficiency disease (infection with human immunodeficiency virus, etc.), diabetes, and a previous abnormal glucose tolerance test or a significantly abnormal ECG test; (3) liver function test (alanine transferase (ALT), aspartate transferase (AST), total bilirubin (TBIL), albumin (ALB), alkaline phosphatase (ALP), and *γ*-glutamyltranspetidase (*γ*-GT)) >1.5 times compared to the upper limit of normal reference values, or abnormal serum creatinine (Cr); (4) use of any medication intended to treat common cold, which may affect the study results; (5) body temperature > 38.5°C; (6) pregnancy or potential pregnancy or lactation; (7) hypersensitivity or allergy to any component of the test drug; (8) current mentally or legally disabled; (9) current or previous admission to other clinical trials within 3 months before enrollment; (10) symptom of paroxysmal sneezing, nasal congestion, or a runny nose are considered allergic diseases by investigators.

To distinguish a cold event from an allergy, the participants who are allergic to or possess contraindications for the use of certain components of the study drugs will be excluded at enrollment. Additionally, all the clinical researchers involved in the study are educated on the difference between common cold and an allergic event and informed to distinguish between these events during enrollment, such that “cold symptoms occur one at a time, generally last for 5–7 days, with yellow/greenish nasal discharge, and may or may not be accompanied by a fever, with slight body aches and pains, but allergic symptoms occur rapidly and all at once and last as long as the allergy-causing agent is present, with clear and watery nasal discharge, not associated with a fever, and with no body aches or pains” [29]. The clinical researchers will also be informed to enquire about the allergic history of each participant and to ask whether the participant has had contact with the allergic components recently.

#### 2.2.4. Withdrawal and Dropout

The study participation will be terminated if the amount of study medication taken is poor (actual usage of trial drug <80% or =120%) or the participant is unable to cooperate with the trial investigators and/or unable to complete the follow-up. When an allergic reaction or a serious adverse event is revealed, a participant is unwilling to continue the trial, or symptoms do not improve or worsen after taking the study drugs for 72 hours, the patient will be withdrawn from the trial after a researcher's assessment, and the data will be considered invalid but will be included in the full analysis set (FAS). If the participant drops out, he or she will be contacted via phone interviews, e-mail, or written letters. The reason for study discontinuation and the last time the medication was taken will be recorded. Participants who exit the trial due to allergies, poor curative effects, or other adverse events will receive appropriate treatment.

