#### 2.1.1. Medicinal Preparations

The main components of SGLNG are shown in Table 1. One gram of SGLNG equals 2.22 g raw plant drugs. Each component of SGLNG is produced by soaking the material in distilled water for 30 minutes, boiling it in 10 volumes of water (v/w) for 1 hour, extracting it with water twice, filtering, and condensing it to the concentration of 1 g/ml and processing it to a fine granular form by spray drying [25]. Considering the characteristics of Chinese herbal medicine, the placebo is prepared by 10-fold dilution of the study drug (SGLNG) and then condensed into granules, which are composed of 10% SGLNG and 90% maltodextrin, and the colour is made identical to SGLNG by adding artificial pigment (tartrazine, sunset yellow, and sucralose). After a 10-fold dilution, the study drug exhibits very little clinical or pharmacological effects and therefore can be used as a placebo [26]. This preparation of placebo has been used in previous studies [16]. SGLNG and placebo are nearly identical in appearance, taste, and scent and dissolve quickly in water. The production and packaging of SGLNG as well as placebo granules are provided by the sponsor unit (Hebei Baishan Pharmaceutical Co. Ltd., Hebei, China). The granules are produced in a single batch (SGLNG batch number Y140501; Placebo batch number Y140501-1). Based on the high performance liquid chromatography techniques, and good manufacturing practices (GMPs) full-range management, this company can guarantee the consistency of granule composition. All drugs are concealed in uniform packages with the same labels except drug numbers, and three bags of the test drug (the dose for one drink) are packed in a small box, with each large box containing 5 plus 1-day dosage (a total of 18 small boxes inside). Participants are isolated from each other after enrollment and are advised to take the drugs at home to avoid chatting about the drugs.

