### 2.5. Interventions

#### 2.5.1. Interventions

Patients who meet the inclusion criteria and none of the exclusion criteria are randomized into one of four treatment groups: (1) high-dose group: 3 bags of SGLNG/time; (2) middle-dose group: 2 bags of SGLNG plus 1 bag of placebo granule/time; (3) low-dose group: 1 bag of SGLNG plus 2 bags of placebo granule/time; and (4) control group: 3 bags of placebo granule/time.

Each participant receives a large box and be instructed to dissolve one small box of the contents in approximately 200 mL of warm liquid and take orally after each meal, 3 times daily for 5 days. The participants are isolated from each other after enrollment and advised to take the drugs at home to avoid discussing the drugs. Participants, researchers, and outcome assessors will remain blinded to the treatment allocation throughout the study.

Throughout the study period, participants will not be permitted to use any other treatments for the common cold, including oral medications and TCM therapies such as cupping, massage, or acupuncture. Medications for concomitant diseases, such as hypertension, are allowed. The dosage, duration, and name of any concomitant medication or treatment will be recorded.

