#### 2.5.2. Follow-Up and Compliance

The follow-up visits will last for 5 days after the treatment. Details of the study procedures are shown in Table 3. During the 11-day study period, a total of four visits (on the 1st, 4th, 6th, and 11th days) will be performed. After the enrollment, the investigators will contact each patient every day to obtain the details of dynamic changes in cold symptoms and remind them to attend the clinical visits on certain dates. The participants are required to collect the packages after taking the granules and bring them on the 4th and 6th days visits. The total actual dose is defined as the total number of bags that are actually used (by counting the number of consumed capsules).

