#### 2.6.4. Compliance Assessment

The compliance of each participant is calculated from the total dose that was actually taken and the total dose required by the study protocol. The total actual dose is defined as the total number of bags that are actually used (by counting the number of consumed capsules), and the total required dose is defined as the number of bags that should be used during the 5-day treatment. Compliance is assessed on the 11th day after the intervention. The formula is as follows:(1)$$\begin{array}{c} Compliance=\frac{Total\;\;actual\;\;dose}{Total\;\;required\;\;dose}\times 100\%. \end{array}$$

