### 2.8. Statistical Analysis

The full analysis set (FAS) is the primary analysis set for efficacy with an intention-to-treat (ITT) principle. In the FAS, all patients will be treated with at least one dose of the study drug and at least one clinical observation will be recorded in the study. All subjects without any major protocol deviations will be involved in the per-protocol set (PPS). The safety analysis will be conducted for randomized subjects who have completed at least one study visit and have safety data. Descriptive statistics will be performed on continuous variables, frequencies, and categorical variables. All symptom durations, total score reductions on Jackson's scale and TCM symptoms, the duration of each TCM symptom, the decreasing rate of TCM main symptoms, and the reduction score of TCM symptoms will be estimated with the Kaplan-Meier technique and compared using the stratified log-rank test. Comparisons among different dose groups and age layers will be conducted with an analysis of variance (ANOVA) and a least significant difference *t*-test. In this multicenter trial, the Cochran-Mantel-Haenszel test stratified by clinical centers and the logistic regression model adjusted for covariates will be used. Statistical analyses will be conducted by an independent statistician from the Health Statistics Department of the Fourth Military Medical University using the SAS statistical software 9.1.3 (SAS, Cary, North Carolina State University, North Carolina, USA).

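### Drug use outside the 80%/120% limits ends study participation, so outcome collection can stop for a post-randomisation reason, and the protocol does not say where these patients stand in the ITT-based FAS

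*Protocol article*

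**What the plan says.** All references are to the protocol article.

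- **Termination rule (2.2.4):** "The study participation will be terminated if the amount of study medication taken is poor (actual usage of trial drug <80% or =120" per cent). The same sentence also ends participation for patients who cannot cooperate or cannot complete follow-up.
- **Retention clause (2.2.4):** the next sentence deals with allergic reaction or serious adverse event, unwillingness to continue, and no improvement or worsening after 72 hours of drug. Only for these does it say that the data, although called invalid, go into the FAS.
- **Denominator (2.6.4):** "the total required dose is defined as the number of bags that should be used during the 5-day treatment". Nothing adjusts it for early recovery.
- **Timing:** participants keep the used packages and "bring them on the 4th and 6th days visits" (2.5.2). Table 3 places drug return and drug count at Visit 3. Section 2.6.4 says: "Compliance is assessed on the 11th day after the intervention".
- **Analysis sets (2.8):** "The full analysis set (FAS) is the primary analysis set for efficacy with an intention-to-treat (ITT) principle". Membership needs one dose and one recorded observation, with no compliance threshold. Major protocol deviations are a bar only to the per-protocol set.

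**The concern.** A compliance limit is an ordinary criterion for a per-protocol set. Here it is a reason to end participation. How much drug a patient takes is decided after randomisation, and in a short, self-limiting illness it may depend on how fast the cold clears, how well the granules are tolerated and whether the patient sees any benefit. All of these can differ by dose. Stopping data collection on such a variable selects patients by something related to outcome, and the comparison of three doses with control relies on randomisation to rule that out.

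Keeping a patient nominally in the FAS does not restore measurements that were never taken. The protocol also does not say that patients terminated for compliance are kept, although it does say so for other withdrawals.

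**Working it through.** **Inputs**

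- Bags per intake: 3, from section 2.1.1 ("three bags of the test drug (the dose for one drink) are packed in a small box").
- Intakes: 3 per day for 5 days, from section 2.5.1 ("take orally after each meal, 3 times daily for 5 days").
- Supply, from section 2.1.1: "with each large box containing 5 plus 1-day dosage (a total of 18 small boxes inside").
- Compliance (2.6.4) = bags used / bags required × 100%.

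**Step 1. The plan's own figure.** (5 + 1) days × 3 boxes = 18 small boxes, as stated. In bags, 18 × 3 = 54.

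**Step 2. The requirement.** 3 bags × 3 times × 5 days = 45 bags, or 15 intakes.

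**Step 3. The limits in intakes.**

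- 80%: 0.80 × 45 = 36 bags = 12 intakes = 4 full days.
- 11 intakes: 33/45 = 73.3%, below the limit.
- 9 intakes (the end of day 3, or 72 hours): 27/45 = 60%, below the limit.
- The whole pack: 54/45 = 120%, exactly the upper limit.

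Anyone who stops before completing four full days of intake meets the rule, whatever the reason.

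**Step 4. The two sections side by side.** A patient with 11 intakes, at least one recorded observation and no other reason for withdrawal is terminated under 2.2.4 without any statement about the FAS, yet qualifies for the FAS under 2.8. A patient withdrawn at 72 hours for non-improvement has 60% use and so meets both sentences of 2.2.4. One sentence keeps that patient in the FAS and the other is silent.

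**Step 5. What is lost depends on when the rule acts.** Section 2.2.4 does not say when that is.

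- *At Visit 3 (day 6 ± 1), when drug is counted:* Visit 4 (day 11 ± 2) does not take place. The day-11 Jackson and TCM total scores are lost; they are one of three post-baseline time points for two of the three primary outcomes (2.6.5). The day-11 curative effect (2.6.6) is lost too. For a patient still symptomatic at Visit 3, so is the rest of the duration follow-up, including the phone or e-mail contact planned beyond day 11.
- *On day 11, when compliance is assessed:* the scheduled visits are complete, so no planned visit is lost. Follow-up of symptoms lasting beyond day 11 could still be cut short.

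**Step 6. Size, under assumptions that the documents do not supply.** Assume log-normal durations with a control median of 5 to 8 days and a log-SD of 0.3 to 0.5, and active durations 0.8 times control. Of the patients recovered by day 3, 25% to 100% stop drug at once and their data are deleted entirely. Then:

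- 0–15% of control and 0–28% of active patients are lost, and the mean difference shrinks by 0–27%.
- At the extreme (control median 5, log-SD 0.5, all stop), the difference falls from 1.13 to 0.82 days: (1.13 − 0.82)/1.13 = 27%.
- A middle case (control median 6, log-SD 0.5, half stop) loses 4.1% and 8.6%, and the difference falls from 1.36 to 1.25 days: 0.11/1.36 = 8%.
- With no true effect there is no bias.
- If the patients stay in the FAS with recovery recorded, the duration comparison does not change.

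**The case against.** A reader might infer that early recoverers are removed from the primary analysis, that the ITT principle is thereby undone, and that the dose comparison is pulled toward no difference. The documents do not support this.

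- **Deletion is not stated.** The FAS definition in 2.8 would admit these patients, and every shrinkage figure in step 6 requires full deletion.
- **Stopping on recovery is inferred.** The regimen is a fixed 5 days. Entry is within 48 hours of onset (2.2.2), and colds are said to last 5–7 days (2.2.3) or 7–10 days (Introduction). Complete recovery before the 12th intake is therefore a short tail.
- **Early recoverers are largely protected on duration.** Symptoms are obtained by daily contact (2.5.2). Recovery by about day 3.7 plus the two zero-score days of 2.6.5 is documented by about day 6, roughly Visit 3. What they would lose is mainly a day-11 score likely to be near zero.
- **The direction is open.** Patients who stop for intolerance or lack of benefit are caught as well. A non-improver withdrawn at 72 hours is at 60%.
- **The timing is not a contradiction.** Drug can be counted at Visit 3 and compliance calculated on day 11.

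All of this stands, and it limits the point to lost follow-up and unstated status. It does not justify ending participation for low use. The last item leaves an ambiguity that matters, because termination at Visit 3 would cost the day-11 primary scores.

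**Conclusion.** The concern holds in a limited form. As written, section 2.2.4 ends participation when use falls below 12 of 15 intakes or meets the upper limit. This is a post-randomisation reason, possibly related to outcome or tolerability, and it sits badly with an ITT-based primary set. Two things follow from the text without any assumption: the FAS status of these patients is stated nowhere, although 2.8 would keep them; and the rule, if applied at Visit 3, leaves day-11 primary scores, the day-11 curative effect and some durations uncollected.

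The documents give neither the frequency of low use nor its causes by arm, so the size and direction of any bias cannot be determined. The 0–27% range illustrates full deletion under assumed durations and is not an estimate for this trial. The correction is still worth making before data are collected, because missed day-11 assessments cannot be recovered afterwards.

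**What to change.** - **Section 2.2.4:** for compliance outside the limits, replace termination of participation with continued outcome follow-up (daily contacts, Visits 3 and 4) whatever the amount of drug used. This concerns data collection only; nothing is proposed about treatment.
- **Section 2.8:** state that these patients stay in the FAS with all their data, and that the 80%/120% limits define only the per-protocol set.
- **Timing:** reconcile 2.2.4, 2.5.2, 2.6.4, 2.8 and Table 3 on when drug is counted, when compliance is calculated and what follows from the result.

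The cost is a sentence in each of 2.2.4 and 2.8 and a clarification of timing. Visits 3 and 4 are already scheduled, so no visits or patients are added. The downside is that the FAS will contain some patients with lower exposure, which ITT implies in any case; the per-protocol set remains available to show the comparison among compliant patients.

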### 2.3. Sample Size Calculation

The sample size was determined using Encyclopaedia Medical Statistics 3.2 software (PEMS 3.2, Guangzhou Jing far Pharmaceutical Research Co., Ltd., Guangzhou, China) with 90% power and a significance level of 0.05 (two-sided). According to Lizogub et al. [30], the sample size should consist of 50 participants in each group. Considering the potential 20% loss, 60 participants are needed for each group. As there is a low-dose group, a middle-dose group, a high-dose group, and a control group with five centers involved, a total of 240 participants will be recruited in this study, with 48 patients recruited at each center.

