#### 2.6.5. Primary Outcomes

*Duration of All Symptoms*. Duration of all symptoms is defined as the number of days from enrollment to the day that all symptoms disappear (the time from the symptom severity score above zero until 2 days of the severity score marked as zero). If symptom severity is marked above zero on the day after a single day of zero, the cold is defined as continuing. If the day marked above zero is the 11th day, this is defined as the end of the cold, but if symptoms last more than 11 days, follow-up will continue via phone call or e-mail until all symptoms are absent. The first day of medication administration is defined as the 1st day (day 1) in the study. The start of the day is defined as 6:00 a.m., and symptoms absent before 6:00 a.m. are regarded as occurring the day before.

Because all the participants in the trial have Qi-deficiency syndrome and normally present certain Qi-deficiency symptoms (fatigue, shortness of breath, and spontaneous perspiration), we define the disappearance of Qi-deficiency symptoms (symptom score = 0) (Table 2) as all the symptoms returning to the basic level present before the onset of common cold.

*The Total Score Reduction of Jackson's Scale*. Jackson's scale [27], which is specific for diagnosis and symptom severity assessment of common cold, contains 8 symptoms (sneezing, headache, malaise, chilliness, nasal discharge, nasal obstruction, sore throat, and cough) and rates as 0 = absent, 1 = mild, 2 = moderate, and 3 = severe. The symptom score will be summed on the 1st day and the 4th, 6th, and 11th days after intervention, and the score reduction will be calculated between the 1st day and the days after the intervention.

The symptom severity and score are assessed by researchers who are blind to the trial, and one participant is assessed by the same researcher consistently throughout trial. Participants will not be allowed to assess their overall illness or level of severity to avoid assessment bias.

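### The 72-hour rule ends trial participation rather than study drug, so later primary-outcome data of patients kept in the FAS may go uncollected because of their symptom course

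*Protocol article*

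**What the plan says.** Section 2.2.4 (Withdrawal and Dropout) groups several reasons for exit: allergic reaction or serious adverse event, unwillingness to continue, and the symptom-based one at issue, "symptoms do not improve or worsen after taking the study drugs for 72 hours, the patient will be withdrawn from the trial". The exit is not automatic; the patient is "withdrawn from the trial after a researcher's assessment". Of such patients the section says "the data will be considered invalid but will be included in the full analysis set (FAS", without explaining how both halves apply. Dropouts are to be contacted by phone, e-mail or letter, and what is to be recorded is named: "The reason for study discontinuation and the last time the medication was taken will be recorded". Patients who leave for poor effect receive appropriate treatment.

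Section 2.6.5 has three primary outcomes. For the Jackson scale, "The symptom score will be summed on the 1st day and the 4th, 6th, and 11th days after intervention", and the reduction is taken from day 1. The TCM scale reduction is due on days 4, 6 and 11 as well. Duration runs from enrollment until all symptoms are gone, with phone or e-mail follow-up beyond day 11 where needed. Section 2.5.2 adds that after enrollment "the investigators will contact each patient every day to obtain the details of dynamic changes in cold symptoms". Section 2.7 lists worsening of symptoms as an adverse event, followed until symptoms disappear. Section 2.8 makes the FAS, on the intention-to-treat principle, the primary efficacy set.

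**The concern.** The trigger for exit is the symptom course, which all three primary outcomes measure. Day 1 is the first day of medication, so 72 hours falls at about visit 2 on day 4. The day-4 score should usually exist, but days 6 and 11 come after exit. The plan thus requires these patients in the primary analysis while ending the participation that would yield their later values.

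If the drug works, fewer active than control patients meet the rule. The controls who remain are then a better-than-average selection, and a comparison of those still observed understates the benefit. For duration, censoring such patients at withdrawal would overstate recovery in the same way, most in control. How missing values are handled can be left to an analysis plan. Whether scores are taken at all is a matter of conduct, and no later analysis recovers a score never recorded.

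**Working it through.** **What is stated after exit**

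| Data | Patients who worsen | Patients who merely fail to improve |
|---|---|---|
| Day-4 score | probably observed (visit 2) | probably observed (visit 2) |
| Day-6 and day-11 scores | not stated | not stated |
| Resolution date | may exist through adverse-event follow-up (2.7) | not stated |

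The contact with dropouts (2.2.4), daily contact (2.5.2) and phone follow-up (2.6.5) do not exclude further collection. None of them states it for withdrawn patients.

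**The plan's own figure.** Section 2.3 gives 90% power, two-sided 0.05, 50 per group, then "Considering the potential 20% loss, 60 participants are needed for each group": 50 × 1.2 = 60. The article gives no effect size. For a two-group t-test, 90% power at 50 per group implies a standardised difference d of about 0.655: d√(50/2) = 3.275, and 3.275 − 1.96 = 1.315, about 90% (90.0% with the t distribution). At 60 per group, 0.655 × √30 = 3.588, and 3.588 − 1.96 = 1.628, about 94.5%. So 94-95% is the correct starting point, because 60 already contains the loss allowance.

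**Assumptions, none of them in the article.** One dose is compared with control. The later score reduction Y has SD 1 and treatment difference d. The 72-hour response X has SD 1 and correlation ρ = 0.3 to 0.7 with Y. Patients with X below a cut-off c, the same in both arms, leave and contribute no later score. The cut-off gives w = 5%, 10% or 20% withdrawal in control. Treatment shifts X by s, taken either as d or as ρd. The automatic cut-off stands in for the researcher's assessment.

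**Formulas.** With λ(a) = φ(a)/(1 − Φ(a)):

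- difference among patients still observed = d − ρ[λ(c) − λ(c − s)]
- variance of Y among those observed in an arm = 1 − ρ²λ(a)[λ(a) − a], with a = c in control and a = c − s in active

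**Worst case worked.** Take w = 20%, ρ = 0.7, s = d.

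- c = −0.842, λ(c) = 0.350; c − s = −1.497, λ(c − s) = 0.140.
- Difference = 0.655 − 0.7 × 0.210 = 0.508, a shrinkage of 22.5%.
- Active withdrawal = Φ(−1.497) = 6.7%, leaving 48 control and 56 active patients.
- Variances are 0.796 and 0.888; SE = √(0.796/48 + 0.888/56) = 0.180.
- 0.508/0.180 = 2.82, and power is about 80%.
- Losing the same numbers at random gives SE = √(1/48 + 1/56) = 0.197, 0.655/0.197 = 3.33, and power about 91%. The remaining 11 points or so come from the selection, not from lost numbers.

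**Range over ρ and both forms of s** (simulated t-tests; the closed form agrees within about one point):

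| Control withdrawal (assumed) | Active withdrawal | Shrinkage of difference | Power at 60 per group |
|---|---|---|---|
| none | none | 0 | 94-95% |
| 5% | 1-3% | 2-8% | 92-93% |
| 10% | 3-7% | 3-14% | 87-92% |
| 20% | 7-15% | 4-23% | 79-88% |

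**Type I error.** With d = 0 and s = 0 the two λ terms cancel and the expected difference is zero. One blinded rule applied alike in all arms does not create a spurious effect.

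No size is put on duration, which would need an assumed distribution and an assumed share of worsening patients followed to resolution. The direction is the same if withdrawn patients are censored at exit.

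**The case against.** The strongest reply is that the loss is inferred from silence in a condensed article. Nothing says that scoring stops at withdrawal, several sections lean towards continued contact, and the patients remain in an intention-to-treat set. This stands as a limit: a reader might infer that the later data will certainly be lost, and the article does not support that. It does not remove the point. The rule that is stated removes the patient from the trial, and the section names what is recorded at exit without mentioning symptom scores.

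A reader might also infer that duration is lost for every withdrawn patient. Section 2.7 does not support that for those who worsen.

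A further reading would be that *invalid* means the data are discarded. The Curative Effect outcome in 2.6.6 uses the same word as the grade for a score reduction below 50%, so the phrase may mean treatment failure. That is not certain either, since the same sentence covers allergy and refusal. The word needs explaining, not deleting.

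On size, every figure assumes available cases, which section 2.8 does not specify. At up to about 10% withdrawal the planned 90% is roughly kept. Recruitment within 48 hours of onset and symptoms that typically peak at days 1-3 suggest that many patients will be improving by 72 hours, and the researcher's assessment may reduce withdrawals further. All of this stands and keeps the harm modest. The 20% allowance, however, covers lost numbers and not a biased difference.

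Finally, scores after rescue treatment answer a treatment-policy question, and counting such patients as failures is also legitimate. That is a choice of analysis. Collecting the scores is needed to keep both options open.

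**Conclusion.** The point holds as a conditional risk written into a conduct rule. Patients who do badly at 72 hours leave the trial but stay in the primary set, and collection of their day-6 and day-11 scores, and of the resolution date for non-improvers, is not stated. If those scores are missing and available cases are analysed, the difference is biased towards no effect by up to about 8%, 14% and 23% at 5%, 10% and 20% assumed control withdrawal. Power falls below the planned 90% mainly when withdrawal is well above 10%. The sizes rest on the assumed rates, correlations and automatic cut-off, and on d = 0.655 back-calculated from 90% power at 50 per group.

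A reader might go further and conclude that the trial is underpowered or prone to a false claim of efficacy. Neither follows: no withdrawal rate is documented, the bias runs against the drug, and type I error is not materially affected. The change is worth making because it is cheap and the missing scores could not be recovered later.

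**What to change.** In section 2.2.4, make the 72-hour rule a stop of study drug with appropriate, recorded treatment, not an end of participation. State that daily contact, day-6 and day-11 scoring on both scales, and phone follow-up to resolution continue for these patients, whether they worsened or only failed to improve. Keep their observed data in the FAS. State whether *invalid* means a treatment failure or exclusion from the per-protocol set. Add a sensitivity analysis that counts these patients as unresolved or as treatment failures.

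The cost is wording, plus contacts and visits already scheduled for every patient; no added sample size is needed. The downside is that later scores may reflect rescue treatment. Section 2.5.1 already provides that "The dosage, duration, and name of any concomitant medication or treatment will be recorded", so this can be described and examined.
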